# Perioperative and long-term outcomes of liver resection for hepatitis B virus-related hepatocellular carcinoma without versus with hepatic inflow occlusion: study protocol for a prospective randomized controlled trial

**DOI:** 10.1186/s13063-016-1621-9

**Published:** 2016-10-11

**Keywords:** Hepatocellular carcinoma, Liver resection, Vascular occlusion, Randomized controlled trial, Ischemia-reperfusion injury, Inflammatory response, Survival

## Abstract

**Background:**

The high prevalence of hepatitis B virus (HBV) imposes a huge burden of hepatocellular carcinoma (HCC) in Asia. Surgical resection remains an important therapeutic strategy for HCC. Hepatic inflow occlusion, known as the *Pringle maneuver*, is the most commonly used method of reducing blood loss during liver parenchymal transection. A major issue with this maneuver is ischemia-reperfusion injury to the remnant liver, and the hemodynamic disturbance it induces in the tumor-bearing liver raises an oncological concern. Given the technical advances in living donor liver transplantation, vascular occlusion in liver resection can be avoided in experienced hands. The aim of this study is to compare the perioperative and long-term outcomes of liver resection for HBV-related HCC without versus with hepatic inflow occlusion.

**Methods/design:**

This study will include eligible patients with HBV-related HCC elected for liver resection. Fifty-seven patients will be enrolled in each randomization arm to detect a 20 % difference in the serum level of total bilirubin on postoperative day 5 (80 % power and α = 0.05). The secondary endpoints include procedural parameters, perioperative liver function and inflammatory response, postoperative morbidity and mortality, and long-term outcomes. Patients will be followed for up to 5 years. Data will be statistically analyzed on an intention-to-treat basis.

**Discussion:**

This prospective randomized controlled trial is designed to compare the perioperative and long-term outcomes of liver resection for HBV-related HCC without versus with vascular occlusion. The clinical implications of these outcomes may change current surgical practice and fill the oncological gaps therein.

**Trial registration:**

Clinicaltrials.gov identifier NCT02563158. Registered on 28 September 2015.

**Electronic supplementary material:**

The online version of this article (doi:10.1186/s13063-016-1621-9) contains supplementary material, which is available to authorized users.

## Background

Hepatocellular carcinoma (HCC) is the fifth most common neoplasm worldwide and the third leading cause of cancer mortality [1]. In China, HCC is the second most common cause of cancer-related death [2], and up to 80 % of HCC cases are attributable to hepatitis B virus (HBV) infection [3, 4].

Surgical resection remains an important therapeutic strategy for HCC [5]. Intraoperative blood loss and requirement for transfusion have been shown to correlate well with perioperative morbidity and mortality [6]. Hepatic inflow occlusion, also known as the *Pringle maneuver*, is traditionally practiced to reduce blood loss during liver parenchymal transection [7]. However, this maneuver induces significant ischemia-reperfusion (IR) injury to the remnant liver, especially in patients with underlying liver disease [8]. In China, hepatitis B virus surface antigen is detected in 70–79 % patients with cirrhosis of the liver [9, 10]. It is widely accepted that the cirrhotic liver is particularly sensitive to IR injury [11, 12]. Furthermore, intermittent application of the Pringle maneuver, a recommended practice, could induce hemodynamic disturbance to the tumor-bearing liver, which raises an oncological concern [13, 14].

In living donor liver transplant (LDLT), liver procurement is performed without hepatic vascular occlusion to reduce the graft warm ischemia time and the IR injury to the donor remnant liver [15, 16]. In recent years, liver resections, even those done for cirrhotic livers, have been performed without vascular occlusion in some centers with expertise [17, 18]. We therefore hypothesize that liver resection for HBV-related HCC (the most common etiology in our region) could be safely performed without vascular occlusion. The present prospective randomized controlled trial (RCT) is designed to compare the perioperative and long-term outcomes of liver resections without and with hepatic inflow occlusion.

## Methods/design

### Trial population

From January 2016 to November 2017, all patients with HBV-related HCC scheduled for elective partial hepatectomy in the Department of Hepatobiliary Surgery, Chinese People’s Liberation Army General Hospital (PLAGH), will be screened for eligibility for this trial.

#### Inclusion criteria

Patients who meet the following criteria will be included in the study:Aged between 18 and 65 yearsElective liver resection for HBV-related HCC with Barcelona-Clínic Liver Cancer stage 0 or A [19]Child-Pugh class A with or without cirrhosis, or reversed to class A from class B after conventional therapyTumors located in either the left or right liver lobeResection extent is a hemihepatectomy or lessInformed consent provided

#### Exclusion criteria

Patients who meet any of the following criteria will be excluded from the study:Having comorbidity that contraindicates surgeryUndergoing intervention as part of other ongoing trials with interference with the present studyHaving undergone nonsurgical interventions that included portal vein ligation/embolization, radiofrequency ablation, and transarterial chemoembolizationScheduled for laparoscopic hepatectomyRequiring concomitant procedures, such as digestive, vascular, or biliary reconstructionLack of compliance with treatment or future follow-up

### Study design

#### Randomization and blinding

Randomization will be performed to achieve comparability in terms of known and unknown confounding variables. The patient allocation will be based on computerized random number generation. All patients eligible for the study will be allocated an opaque envelope marked only with the patient-specific random number. The decision regarding the procedure performed will be sealed inside. The envelope will be opened right before the preoperative instruction for surgery is given to the patient, and then the patient will be automatically assigned to group A (with hepatic inflow occlusion) or group B (without hepatic inflow occlusion). Owing to the nature of surgery and the patient’s right of informed consent, neither the surgeons nor the patients can be blinded to the procedural details. Only the trial coordinators will be blinded to the information regarding patient allocation during data processing and analysis.

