#### Follow-up

Patient follow-up will start upon discharge from the hospital. All patients are required to visit their surgical team in person 3 and 6 months as well as 1, 2, 3, and 5 years after surgery or whenever necessary. Routine checkups, including abdominal ultrasound, CT and/or MRI, and serum biochemistry and AFP will be performed at each visit. Checkup data from qualified local hospitals will also be acceptable.

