PHLF	Increased INR (or need of clotting factors to maintain normal INR) and hyperbilirubinemia on or after POD 5; if INR or serum bilirubin concentration is increased preoperatively, PHLF is defined by increasing INR and bilirubin concentration on or after POD 5 (biliary obstruction should be ruled out); graded according to ISGLS [26] as follows: A: PHLF requiring no or little change in patient’s clinical management B: PHLF resulting in deviation from regular clinical management but manageable without invasive treatment C: PHLF requiring invasive treatment
Bile leakage	Increased bilirubin concentration (at least three times greater than the serum level measured at the same time) in abdominal drain or intraabdominal fluid on or after POD 3, or as need for radiological intervention (e.g., interventional drainage) because of biliary collections or relaparotomy resulting from bile peritonitis; graded according to ISGLS [39] as follows: A: Bile leakage requiring no or little change in patient’s clinical management B: Bile leakage requiring change in patient’s clinical management (e.g., additional diagnostic or interventional procedures) but manageable without relaparotomy, or a grade A bile leakage lasting >1 week C: Bile leakage requiring relaparotomy
Posthepatectomy hemorrhage (PHH)	Evidence of intraabdominal bleeding such as frank blood loss via the abdominal drains (e.g., hemoglobin level in drain fluid >3 g/dl) or detection of intraabdominal hematoma or active hemorrhage by abdominal imaging (ultrasound, CT, angiography); graded according to ISGLS [40] as follows: A: PHH requiring transfusion of ≤2 U of PRBCs B: PHH requiring transfusion of >2 U of PRBCs but manageable without invasive intervention C: PHH requiring radiological interventional treatment (e.g., embolization) or relaparotomy
Intraperitoneal effusion/abscess	Any imaging-detected intraperitoneal fluid collection and/or elevation of infectious parameters (CRP >2 mg/dl and/or leukocytes >100,000/ml), positive physical signs, and bacteriology of abdominal drainage
Pulmonary infection	Elevation of infectious parameters (CRP >2 mg/dl and/or leukocytes >100,000/ml) and/or evidence of pulmonary infiltration on chest x-ray requiring antibiotic therapy
Postoperative ICU/hospital stay	Time from day of operation through discharge from ICU and/or hospital (days)
Total in-hospital expenditure	Costs from admission to discharge (¥/$)
Mortality	In-hospital death and 90-day death.
Long-term outcomes	

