Survival	1-, 3-, and 5-year overall and disease (tumor)-free survival
Tumor recurrence	Identification of the typical hallmarks of recurrent HCC foci by dynamic imaging (CT/MRI) plus AFP >400 ng/ml in suboptimal settings (e.g., foci <2 cm) [24]

*Abbreviations: AFP* Alpha-fetoprotein, *ALB* Albumin, *ALT* Alanine aminotransferase, *AST* Aspartate aminotransferase, *CRP* C-reactive protein, *CT* Computed tomography, *HCC* Hepatocellular carcinoma, *ICU* Intensive care unit, *IL* Interleukin, *INR* International normalized ratio, *ISGLS* International Study Group of Liver Surgery, *MRI* Magnetic resonance imaging, *PCT* Procalcitonin, *PHH* Posthepatectomy hemorrhage, *PHLF* Posthepatectomy liver failure, *POD* Postoperative day, *PRBCs* Packed red blood cells, *PT* Prothrombin time, *TBil* Total bilirubin, *TNF-α* Tumor necrosis factor-α

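### No arm-blind assessment is planned for recurrence, disease-free survival or graded complications, although the reason given for an open trial covers only surgeons and patients

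*Protocol article*

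**What the plan says.** Under Randomization and blinding, the article explains that "neither the surgeons nor the patients can be blinded to the procedural details", citing the surgical nature of the intervention and informed consent. It then says: "Only the trial coordinators will be blinded to the information regarding patient allocation", and confines even this to the stage at which data are processed and analyzed.

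Under Follow-up, "All patients are required to visit their surgical team in person" at 3 and 6 months and at 1, 2, 3 and 5 years, or when needed in between. What is collected is also fixed there: "Routine checkups, including abdominal ultrasound, CT and/or MRI, and serum biochemistry and AFP will be performed at each visit". Results from elsewhere may be used: "Checkup data from qualified local hospitals will also be acceptable".

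In Table 1 (Secondary endpoints), tumor recurrence is defined as "Identification of the typical hallmarks of recurrent HCC foci by dynamic imaging", with an AFP threshold added in less clear settings. Complications are graded by Clavien-Dindo and, for liver failure, bile leakage and hemorrhage, by ISGLS. The grade B entry for liver failure, for example, reads "PHLF resulting in deviation from regular clinical management but manageable without invasive treatment".

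Data management and quality assurance calls the trial unmasked and lists unfair evaluation among the risks. The safeguard it offers is training of surgeons, statisticians and coordinators. No section names the person who reads follow-up scans or grades complications.

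**The concern.** The reason given for an open trial applies to those who operate and those who are operated on. It does not apply to a person reading a CT or MRI months later, or to a person assigning a complication grade. Because the blinding sentence is restricted to the coordinators, this looks like a stated choice rather than a detail left to a longer document.

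The exposed endpoints carry the oncological part of the trial. Long-term outcomes are in the title and the aim. The Discussion states a directional expectation that resection without occlusion may have long-term oncological benefit, and that the results may change practice. If borderline lesions or borderline complications are judged with the arm known, results can drift toward that expectation. A reader of the final report could not separate such drift from a treatment effect on recurrence, disease-free survival or complication grade.

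**Working it through.** **Step 1: who is blinded, set against who could assess.**

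| Item | Where stated | Knowledge of the arm |
|---|---|---|
| Surgeons, patients | Randomization and blinding | Known |
| Trial coordinators | Randomization and blinding; Data management | Blinded during processing and analysis; they enter data and have no patient contact |
| Follow-up visits | Follow-up | Held by the surgical team, so known |
| Scan readers, including local hospitals | Not named | Not stated |
| Complication graders | Not named | Not stated |

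The first three rows are statements in the article. The last two are gaps. Since blinding is confined to the coordinators, no blinded reader or grader is provided for.

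**Step 2: which endpoints depend on judgement.**

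- Primary endpoint, total bilirubin on postoperative day 5: a laboratory value, little exposed.
- Other serum markers, overall survival, in-hospital and 90-day mortality: little exposed.
- Recurrence rate and disease-free survival: exposed through the imaging reading.
- ISGLS grades: exposed through decisions of the treating team (change in management, transfusion, intervention). Clavien-Dindo grading likewise has no blinded grader.

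**Step 3: illustrative size.** The plan gives no figure on this point, so there is none to reproduce. The only input from the documents is 57 per arm (Sample size calculation). The complication rate, the shifts, the hazard ratio and the event counts below are assumptions. There is no true difference in any row, and the test is two-sided at 0.05.

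False-positive rate = P(Z > 1.96 − d) + P(Z < −1.96 − d), where d = bias / SE.

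*Complications*, assumed true rate 15% in both arms, with grading shifted in one arm:

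SE = √(2 × 0.15 × 0.85 / 57) = 0.067

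- Shift of 0.05: d = 0.75, false-positive rate 11.6%
- Shift of 0.03: d = 0.45, false-positive rate 7.3%

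Taking the variance at the shifted rate in the affected arm changes these to 10.8% and 7.2%.

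*Recurrence*, assumed apparent hazard ratio 1.2 from detection alone (log 1.2 = 0.182), SE of log hazard ratio = 2/√events:

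- 40 events: SE = 0.316, d = 0.58, false-positive rate 8.9%
- 80 events: SE = 0.224, d = 0.82, false-positive rate 12.9%

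With 2 × 57 = 114 patients, 40 to 80 events means 35% to 70% with an event.

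**Step 4: what is already collected.** Imaging and AFP are scheduled at every visit, so an arm-blind recurrence call needs no new scan, visit or change in sample size. Drain-fluid bilirubin appears only in the bile-leakage definition and in no listed schedule. Total bilirubin after day 5 is not in the serial list either.

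**The case against.** **The article is condensed and never says who reads scans.** A fuller protocol could name the reader, and local-hospital staff may not know the arm. The blinding sentence can also be read as being about data handling alone. This stands in part. A reader might infer that recurrence and complications *are* assessed by people who know the arm. The documents do not support that: no assessor is named, and nothing says imaging requests show the allocation. What remains is that blinding is expressly confined to the coordinators, so none is planned for assessors.

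**Blinded assessment is not free.** A reader might also infer that existing staff and data could supply it at no cost. The documents do not show this. The coordinators are not described as qualified to read scans or grade complications. They also work from CRFs and records, where conversion to occlusion is noted. The article gives no costs, and it accepts check-up data from local hospitals without saying that images are supplied. This objection stands.

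**Complications could be made objective by using only their laboratory criteria.** This should not be adopted. It would drop the clinical routes in the definitions: clotting factors needed to hold INR normal for liver failure, and intervention or relaparotomy for bile leakage. Some of the laboratory values are in no listed schedule. The management-based grades would still be unblinded.

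**The sizes are hypothetical, and the trial acknowledges the risk.** Both are true. The calculation shows what an assumed bias would do, not that one is likely. The acknowledged safeguard, training, does not remove knowledge of the arm.

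**Conclusion.** The point holds as a limited design weakness. No arm-blind assessment is planned for recurrence, hence disease-free survival, or for graded complications, and the stated reason for an open trial does not extend to those assessors. Whether they will in fact know the arm cannot be told from the article.

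The reach is confined to some secondary endpoints. The primary comparison, overall survival and mortality are little affected. The false-positive rates of about 7% to 13% rest wholly on the assumed rate, shifts, hazard ratio and event counts. They show that modest drift would matter at this sample size and are not estimates for this trial. The change is worth making because the recurrence part can be improved with little work, but it does not threaten the main result.

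**What to change.** Add to Randomization and blinding:

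1. Requests for follow-up imaging carry no allocation.
2. Whoever routinely reports the scan does so without access to the allocation.
3. Recurrence for the analysis (yes/no, and the imaging date) is taken from that report and entered on the CRF.

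Keep the ISGLS and Clavien-Dindo definitions as written. State that grades which depend on management are open-label assessments, and report them as such.

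The cost is one CRF item and some handling of reports from local hospitals, where masking can be requested but not guaranteed. Sample size, visit schedule and treatment are unchanged, and no extra reader is needed. Two limits remain: the medical record can still reveal the arm to someone who looks, and unscheduled visits are arranged with the surgical team, which knows the arm.

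The change was still useful when the article appeared. Trial status reports 26 enrolled by September 2016 against a target of 134 (26/134 = 19%), with follow-up to 5 years, so most recurrence readings lay ahead.

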#### Withdrawal

Participants can withdraw at any time during the trial at their own or their legal representative’s request. A participant may also be withdrawn if, on the basis of the investigators’ judgment, continuation of the trial may be detrimental to the participant’s health. Reasons for all withdrawals will be recorded in patients’ medical files and their case report forms (CRFs). All data will be analyzed according to the intention-to-treat principle [20].

#### Ethics, study registration, and consent

The study protocol was approved by the PLAGH Medical Ethics Committee (S2015-081-01) and is registered in the ClinicalTrials.gov protocol registration system (NCT02563158). The study procedure, benefits, risks, and data management will be introduced in detail to all eligible participants before they are asked to provide written informed consent.

### Surgical interventions

#### Preoperative evaluation

Preoperative management will include imaging studies and laboratory serum tests (see Endpoints section below). Other virological and oncological tests to be performed include HBV antigens, antibodies, and DNA; hepatitis C virus antibody; serum alpha-fetoprotein (AFP); carcinoembryonic antigen; and carbohydrate antigen 19–9. The Child-Pugh grades for liver function will be determined on the basis of serum parameters and the absence or presence of ascites and hepatoencephalopathy [23]. The diagnosis of HCC will be based on the identification of typical radiological hallmarks of HCC (hypervascular in the arterial phase with washout in the portal venous or delayed phase) by four-phase multidetector computed tomography (CT) or dynamic contrast-enhanced magnetic resonance imaging (MRI) [5]. According to the practice recommended by the Ministry of Health of the People’s Republic of China [24], a more conservative approach with two imaging techniques or one technique plus AFP ≥400 ng/ml will be recommended in some suboptimal settings, such as when the nodule is <2 cm in diameter. Advanced imaging such as positron emission tomography will be performed in cases of suspicion of extrahepatic metastases.

#### Surgical procedures

The same group of surgeons with experience of over 3000 hepatectomies and 200 LDLTs will perform all the procedures. The abdominal cavity will be opened through a J-shaped subcostal incision and carefully searched for peritoneal seeding and extrahepatic metastases. After the liver is mobilized, an intraoperative ultrasound will be routinely performed to confirm preoperative findings and double-check the tumor and vascular anatomy.

#### Group A: liver resection with hepatic inflow occlusion

Liver resection will be carried out using the Pringle maneuver to occlude vascular inflow in cycles of 15 minutes of clamping plus 5 minutes of unclamping of the hepatoduodenal ligament. An elastic tourniquet will be used to encircle and tighten the hepatoduodenal ligament to occlude the hepatic blood inflow. A clamp will be used to fix the tourniquet. During parenchymal transection, a hybrid application of electronic cautery, cavitron ultrasound surgical aspirator, titanium clips, and silk ligation will be practiced in an institutional permutation. To reduce bleeding from the hepatic venous system, <5-mmHg central venous pressure will be maintained with the patient in a feet-down tilt position and with volume restriction [25]. After parenchymal transection, an argon beam coagulator will be used for hemostasis of the transection surface. Double-drains to the liver bed will be routinely placed.

#### Group B: liver resection without hepatic inflow occlusion

The procedural techniques used in group B will be same as those in group A, but without vascular occlusion. For the sake of comparability between groups and in cases of problematic bleeding, the hepatoduodenal ligament will still be encircled with an elastic tourniquet. Unplanned conversion from the nonocclusion group to the occlusion group and its cause will be recorded in the patient’s CRF and medical record.

#### Postoperative management

All patients will be transferred to the intensive care unit (ICU) of the PLAGH Department of Hepatobiliary Surgery for early postoperative monitoring. Any subsequent need for an ICU stay will depend on patient-specific status. Postoperative serum parameters will be monitored on a serial basis (see Endpoints section below).

